### Ethical considerations

Ethical approval has been obtained from the Conjoint Health Research Ethics Board (Project ID: E-24846) at the University of Calgary as well as Health Canada (UC-NEPH-2012001) for all study sites involved in the trial. Two external bodies, a Data Safety Monitoring Board and a Trial Steering Committee, will monitor study progress.

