**Standard deviation of the average**	
**Normal wave (SDANN)**	Average of the variation (in units of standard deviation) between each successive R-wave when comparing multiple 5-minute sections of the ECG recording
**Percentage of normal wave variation (pNN50%)**	Percentage of normal R-waves that differ from the wave directly before it by ≥50 milliseconds

The specific physiological parameters which will be assessed at each study visit throughout the study are described in Table 3. A MEDRIO electronic database (http://www.medrio.com) will be utilized for data entry after collection at baseline and every 6 weeks up to 24 weeks. Holter application and simultaneous blood draws will be collected at each study visit in order to observe potential vitamin D therapy-dependent changes in cardiac autonomic tone, circulating renin-angiotensin system activity markers, and mineral metabolism parameters related to vitamin D metabolism including serum calcium, phosphate, and parathyroid hormone. Blood samples collected from subjects at each study day are sent to the on-site laboratory typically used for other routine blood work at each of the study locations. Database access and ability to update blinded data will be provided only to the primary investigators.

**Table 3 T3:** Baseline and ongoing data collection

**Screening visit**	• Age, sex, target weight, duration on dialysis, cause of end-stage kidney disease, vascular access type
	• Serum calcium, phosphate, parathyroid hormone, Kt/V, 25-hydroxy vitamin D, 1,25-dihydroxy vitamin D
	• Medication use
	• GODIN leisure-time activity questionnaire
	• DASI aerobic capacity questionnaire
**Baseline study visit**	• Serum calcium, phosphate, parathyroid hormone, Kt/V, 25OHD level, 1,25-dihydroxy vitamin D level, catecholamines
	• Renin, aldosterone, angiotensin II
	• Delivered dose of dialysis (Kt/V)
	• Power spectral analysis (LF, HF, LF:HF) and time domain (SDNN, SDANN, pNN50%) HRV parameters
**Study visits every 6 weeks up to 24 weeks**	• Serum calcium, serum phosphate, parathyroid hormone, 25OHD, 1,25-dihydroxy-vitamin D, catecholamines
	• Renin, aldosterone, angiotensin II
	• Delivered dose of dialysis (Kt/V)
	• Power spectral analysis (LF, HF, LF:HF) and time domain (SDNN, SDANN, pNN50%) HRV parameters

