### Secondary outcomes

The secondary outcomes include additional measures of cardiac autonomic tone, including LF, HF, as well as time domain parameters of HRV including the standard deviation of the normal R-R interval (SDNN), standard deviation of the average normal R-R interval (SDANN), percentage of normal R waves occurring ≥ 50 ms after the R waves immediately before (pNN50%), as well as blood draw measurements related to vitamin D metabolism at the beginning and termination of each 6 week treatment block (Table 2).

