### Subject follow-up procedures

Subjects will be followed from trial entry until study completion (24 weeks study period). The study coordinator will review each subjects’ collected data at 6 week intervals to record primary and secondary endpoints, as well as to assess the safety and efficacy of the vitamin D administration in relation to study blood work. Study medication may be discontinued for reasons associated with concern for subject safety, or as requested by the subject or primary nephrologist.

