### Study withdrawal

Given that the primary and secondary outcomes require the measurement of cardiac autonomic tone with a Holter monitor, follow up for these outcomes can only occur if the subject is alive and accessible for monitoring. Therefore, subjects will be censored and withdrawn from follow-up under the following circumstances; subject or primary nephrologist request, transfer to peritoneal dialysis, kidney transplantation, transfer of subject to a non-study hemodialysis unit, hospitalization, or death. Upon withdrawal from the study, any data collected up to that time will be utilized in a last observation carried forward (LOCF) approach.

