### Sample size calculation

While we are not aware of any studies examining the use of vitamin D on the primary outcome of this study, previous work by Kontopoulous et al. [47] has demonstrated that post-myocardial infarction (MI) patients (n = 25) randomized to receive 5–10 mg of quinapril (angiotensin converting enzyme inhibitor) per day for 35 days immediately following an MI displayed a 46% reduction in LF:HF from baseline to 6 weeks (mean ± SE: 10 ± 0.7; 5 ± 0.5), while those randomized (n = 25) to receive 50–100 mg of metoprolol per day for 35 days following an MI displayed a similar 36% reduction in LF:HF from baseline to 6 weeks (mean ± SE: 9 ± 0.6; 6 ± 0.4). As such, given that 1) vitamin D deficiency is the norm in hemodialysis patients, 2) vitamin D downregulates the renin-angiotensin system [24,25,35], and 3) increased RAS activity is associated with alterations in cardiac autonomic tone [35-37], we feel there is sufficient justification for the sample size calculation herein**.** Based on these observations, we estimate the standard deviation of the pooled difference in LF:HF from both treatment sequences as 4.53. Using a 2 × 2 crossover design (2 sequences or treatment orderings and 2 time periods or occasions) and anticipating a 20% or larger reduction in LF:HF observed after 6 weeks of treatment with combined vitamin D vs. the reduction observed after 6 weeks of treatment with alfacalcidiol alone, we estimate that 54 subjects will be required (α = 0.05, β = 0.9). In anticipation of a 10% dropout rate, approximately 60 subjects in total will be recruited.

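### Read as written, the LOCF rule gives a patient withdrawn mid-block a false zero change in calcium, phosphate and PTH; the likely bias is small and cheap to remove

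*Protocol article*

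**What the plan says.** All references are to the protocol article.

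- **Rule.** Under Study withdrawal, "any data collected up to that time will be utilized in a last observation carried forward (LOCF) approach". The same paragraph gives the reasons for withdrawal: "subject or primary nephrologist request, transfer to peritoneal dialysis, kidney transplantation, transfer of subject to a non-study hemodialysis unit, hospitalization, or death". It opens by saying that the primary and secondary outcomes need a Holter recording.
- **Laboratory outcomes.** Secondary outcomes lists the HRV measures and then adds "blood draw measurements related to vitamin D metabolism at the beginning and termination of each 6 week treatment block". Data collection describes "mineral metabolism parameters related to vitamin D metabolism including serum calcium, phosphate, and parathyroid hormone".
- **Schedule.** Data collection places study draws at baseline and every 6 weeks to week 24. Primary outcome fixes the blocks as weeks 0 to 6 and 18 to 24. No draw inside a block, and none at withdrawal, is described.
- **Safety.** The Abstract says that the safety of the two regimens will be assessed. Subject follow-up procedures has the coordinator review data at 6-week intervals, "as well as to assess the safety and efficacy of the vitamin D administration in relation to study blood work". The Vitamin D background lists high calcium, high phosphate and lowered PTH as a main clinical concern with activated vitamin D.
- **Dropout.** Sample size calculation: "In anticipation of a 10% dropout rate, approximately 60 subjects in total will be recruited".

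**The concern.** Each block has one laboratory value before dosing and one on treatment. For a patient who leaves in between, the last observation is the pre-dosing one. Carrying it forward records no change on a regimen that the patient did take, whatever the true calcium, phosphate or PTH was at that moment.

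Some of the withdrawal reasons (nephrologist request, hospitalization, death) could follow from a laboratory abnormality. In those cases the patients with the largest changes would be entered as unchanged. Both regimens give the same alfacalcidiol dose, so a laboratory difference between them would come from the ergocalciferol. That difference is diluted if the regimen with the larger change also loses more patients mid-block.

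What is at stake is the analysed laboratory result, and so how far the trial's safety statement can be relied on.

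**Working it through.** **1. The plan's own figure.** 54 / (1 − 0.10) = 60, and 0.10 × 60 = 6 planned dropouts. The article's numbers agree with each other.

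**2. What LOCF carries.** Draws are at weeks 0, 6, 12, 18 and 24; dosing is in weeks 0–6 and 18–24.

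- Withdrawn in weeks 0–6: the week 6 slot receives the week 0 value (pre-dosing), so the block 1 change is 0.
- Withdrawn in weeks 18–24: the week 24 slot receives the week 18 value (pre-dosing, after washout), so the block 2 change is 0.

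The article does not say whether a second block that was never started is also filled. If it were, the week 24 slot would hold a week 0 pre-dosing value (left in weeks 0–6), the other regimen's week 6 value (left in weeks 6–12) or a week 12 washout value (left in weeks 12–18). This case is not counted in the sizes below.

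**3. How many withdrawals fall in one regimen's block.** Each patient is scheduled to spend 6 of 24 weeks on a given regimen. If the 6 dropouts are spread evenly over time (assumption), 6 × 6/24 = 1.5 fall there. The ceiling under the planned dropout is 6.

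**4. Mean laboratory change.** Set the completers' mean change to 1. Let w patients of 60 withdraw in the block, with a true mean change of m (m is assumed; the article gives no laboratory changes).

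- True mean = ((60 − w) + w·m) / 60
- LOCF mean = (60 − w) / 60
- Missing-only mean = 1 (block-end value left missing, completers analysed)

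| w | m | True | LOCF | LOCF too low by | Missing-only too low by |
|---|---|---|---|---|---|
| 1.5 | 1 | 1.000 | 0.975 | 2.5% | 0% |
| 1.5 | 2 | 1.025 | 0.975 | 4.9% | 2.4% |
| 1.5 | 3 | 1.050 | 0.975 | 7.1% | 4.8% |
| 6 | 1 | 1.0 | 0.9 | 10% | 0% |
| 6 | 2 | 1.1 | 0.9 | 18% | 9% |
| 6 | 3 | 1.2 | 0.9 | 25% | 17% |

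For example, with w = 1.5 and m = 3, 1 − 0.975/1.050 = 7.1% and 1 − 1/1.050 = 4.8%.

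**5. Out-of-range counts.** Assume that 10% of completers are out of range at block end, and that k patients withdraw while out of range after an in-range pre-dosing value.

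- k = 3: LOCF 0.10 × 57/60 = 9.5%; missing-only 10.0%; block-end or stopped (5.7 + 3)/60 = 14.5%.
- k = 6: LOCF 0.10 × 54/60 = 9.0%; missing-only 10.0%; block-end or stopped (5.4 + 6)/60 = 19.0%.

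The gap between LOCF and the combined count is k/60: 5.0 points for k = 3 and 10.0 for k = 6. LOCF itself contributes 10.0 − 9.5 = 0.5 and 10.0 − 9.0 = 1.0 point. The remaining 4.5 and 9.0 points arise because stops are not counted, which dropping LOCF alone would not cure.

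**The case against.** **The rule may be meant for Holter outcomes only.** The paragraph's stated reason is that follow-up needs a Holter, and blood tests do not. Statistical analysis states no laboratory comparison; calcium, phosphate and PTH appear there as effect modifiers in the model for autonomic tone. This stands in part: the extension to laboratory values is an inference from the general wording of the rule and from the list of secondary outcomes. But the article gives no other rule for these outcomes, so a reader following it would apply LOCF to them.

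**Laboratory-driven cases may take another route.** Subject follow-up procedures says: "Study medication may be discontinued for reasons associated with concern for subject safety, or as requested by the subject or primary nephrologist". Stopping the drug is not itself listed as withdrawal, so such a patient can still have a real block-end draw. A withdrawal prompted by the 6-weekly review comes after the block-end value is recorded. A mid-block laboratory withdrawal would need results from outside the study draws, for which the article gives neither analytes nor frequency. This stands, and lowers the likely number affected.

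**The dropout covers the whole trial.** The 10% applies to 24 weeks, and transplantation, transfer to peritoneal dialysis and change of unit have no evident link to laboratory harm. This stands; it is why 1.5 is a more reasonable working figure than 6.

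**Patients are protected by other means.** Nephrologists can intervene, and two external bodies, "a Data Safety Monitoring Board and a Trial Steering Committee, will monitor study progress". This is accepted: the point concerns the analysed result only.

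**Conclusion.** The point holds in a limited form. Applied as written to the laboratory secondary outcomes, LOCF enters an untreated value as the on-treatment result of a patient withdrawn mid-block and biases that regimen's mean change toward zero. The likely size is an understatement of about 2.5% to 7%. This rests on the planned dropout, an even spread over time, and withdrawn patients changing one to three times as much as completers. The 10% to 25% range requires all six dropouts to fall within one regimen's block.

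A reader might infer that LOCF could hide up to 10 percentage points of laboratory harm. The documents do not support that. The figure needs all six dropouts in one regimen's block, each out of range after an in-range start, and in the illustration LOCF itself accounts for only 1 of those 10 points. Nor do they show that any patient will be withdrawn mid-block for a laboratory reason, or that unstarted blocks will be filled. The number affected could be zero.

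This is a low-cost clarification worth making, with no bearing on the sample size.

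**What to change.** Add one sentence to the missing-data rule: a pre-dosing, washout or other-regimen laboratory value is not carried into an on-treatment slot, and the block-end value is treated as missing.

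Beside the block-end values, report by regimen how many patients discontinued study drug or were withdrawn for a laboratory reason. Add a reason field to the drug administration schedules and checklists already kept (Randomization and blinding). If LOCF was meant only for the Holter outcomes, the same sentence can say so.

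**Cost.** No extra draws or visits. Slightly fewer patients have paired laboratory values: 60 − 6 = 54 of 60 at worst under the planned dropout. Treating values as missing still understates the mean change if withdrawn patients differ from completers (2.4% to 4.8% with 1.5 withdrawals and a two- to threefold change; up to 17% at the ceiling), so the count of laboratory-driven stops has to stand next to it.

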### Statistical analysis

The primary analysis will test associations between intensive and conventional vitamin D therapies and observed fluctuations in LF:HF from baseline to 6 weeks later within each treatment block utilizing a non-parametric paired t-test. To further determine the relationships between cardiac autonomic tone and specific vitamin D therapy regimens, we will use a repeated measurements analysis of variance model to account for the cross-over design of the study utilizing Greenhouse-Geisser correction values to account for multiple comparisons. Treatment, treatment period, and treatment sequence will be analyzed as fixed effects within the model, as well as additional effect modifiers (gender, vitamin D, calcium, phosphate, parathyroid hormone). Additional analyses will include a subgroup analysis for those subjects with diabetes mellitus as diabetes has been shown to alter parameters of cardiac autonomic tone and vitamin D metabolism [9,21].

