### Primary outcome

The primary outcome of the study is sympathovagal balance (LF:HF), interpreted as the overall balance on stimulatory and inhibitory cardiac autonomic control, from baseline to the final study day within each 6 week treatment block (0 and 6 weeks, 18 and 24 weeks). Comparison of measured sympathovagal balance throughout each of the vitamin D supplementation treatment blocks as well as the 12-week washout period will allow for statistical interpretation of whether presence or absence of oral vitamin D therapy alters cardiac autonomic function within this population. An improvement in sympathovagal balance can be interpreted by a downward shift in LF:HF, in which a smaller value indicates greater contribution of cardioprotective vagal activity (Table 2).

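### The primary contrast subtracts each block's baseline LF:HF in full; using the two collected baselines as a covariate would be more precise

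*Protocol article*

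**What the plan says.** The Primary outcome section defines sympathovagal balance "from baseline to the final study day within each 6 week treatment block (0 and 6 weeks, 18 and 24 weeks"), so each subject contributes two within-block changes. The Statistical analysis section compares "observed fluctuations in LF:HF from baseline to 6 weeks later within each treatment block" between the two regimens "utilizing a non-parametric paired t-test". A paired test of this kind has no place for a covariate.

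A repeated-measures analysis of variance follows. Its listed terms are these: "Treatment, treatment period, and treatment sequence will be analyzed as fixed effects within the model", together with "additional effect modifiers (gender, vitamin D, calcium, phosphate, parathyroid hormone"). Baseline LF:HF is not among them. Both block baselines are nevertheless measured, at weeks 0 and 18.

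**The concern.** In a crossover, stable differences between subjects already cancel when a subject's two block-end values are compared. Subtracting a separate baseline from each brings in two more noisy Holter measurements and forces their coefficient to be 1. If a subject's baseline difference predicts the block-end difference only weakly, most of what is subtracted is noise. Estimating the coefficient removes only the part that is predictive.

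What is at stake is precision in a trial of 54 to 60 subjects. The effect size is borrowed from cardiac drugs after myocardial infarction, because the authors knew of no study of vitamin D on this outcome.

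**Working it through.** **1. The plan's own figure.** The Sample size calculation section states: "we estimate the standard deviation of the pooled difference in LF:HF from both treatment sequences as 4.53", "anticipating a 20% or larger reduction in LF:HF observed after 6 weeks of treatment with combined vitamin D", and "we estimate that 54 subjects will be required (α = 0.05, β = 0.9"). Three readings are needed: β = 0.9 means 90% power, the test is two-sided, and 20% means an absolute difference of 2.0 (20% of the baseline of 10 in the cited post-infarction trial). Then n = ((1.960 + 1.282) × 4.53 / 2.0)² = 53.9, so 54, and 54/0.9 = 60. Both stated numbers reproduce.

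**2. Variances.** For one subject, let B be the difference between the two block baselines (weeks 0 and 18) and E the difference between the two block-end values (weeks 6 and 24). Give both variance V and let their correlation be r.

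- Unadjusted block-end contrast: Var(E) = V
- Planned change contrast: Var(E − B) = 2V(1 − r)
- Baseline-adjusted contrast: Var(E given B) = V(1 − r²)
- Adjusted ÷ change: (1 − r²) / [2(1 − r)] = (1 + r)/2

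**3. Size.** The documents give no r. The range below is an assumption.

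| r | Adjusted ÷ change variance | Fall in SE |
|---|---|---|
| 0 | 0.50 | 29% |
| 0.3 | 0.65 | 19% |
| 0.5 | 0.75 | 13% |
| 0.7 | 0.85 | 8% |
| 0.9 | 0.95 | 2.5% |

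The value r = 0 arises when all four visits are equally correlated. If correlation instead decays with time, with ρ the correlation over 6 weeks, then r = (2ρ − ρ² − ρ⁴) / [2(1 − ρ³)]. For ρ from 0.3 to 0.9 this gives r from 0.26 to 0.62, a variance ratio of 0.63 to 0.81, and a fall in SE of about 21% to 10%.

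**4. Cost of estimating the slope.** A simulation with 54 subjects (27 per sequence, 20,000 runs) gave change ÷ adjusted variance ratios of 1.96, 1.51, 1.31, 1.16 and 1.03 at r = 0, 0.3, 0.5, 0.7 and 0.9. Theory gives 2.00, 1.54, 1.33, 1.18 and 1.05. The difference is about 2% of variance. At r = 0.95 the ratio was 1.00 and the gain had gone.

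**5. What this means for power.** The section does not say whether 4.53 is the SD of the difference of changes or of the block-end difference. The figures below use the normal approximation and a difference of 2.0.

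*If 4.53 is the SD of the difference of changes*, the planned contrast has 90% power with 54 subjects, and the adjusted SD is 4.53 × √[(1 + r)/2]:

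| r | Adjusted SD | Subjects for 90% power | Power at 54 |
|---|---|---|---|
| 0 | 3.20 | 27 | 99.6% |
| 0.3 | 3.65 | 36 | 98.0% |
| 0.5 | 3.92 | 41 | 96.3% |
| 0.7 | 4.18 | 46 | 94.1% |
| 0.9 | 4.42 | 52 | 91.4% |

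*If 4.53 is the SD of the block-end difference*, the change contrast has SD 4.53 × √[2(1 − r)]. At 54 subjects its power is 63% at r = 0, 78% at r = 0.3, 90% at r = 0.5 and 98.7% at r = 0.7. The adjusted contrast has 90%, 92.5%, 96.3% and 99.5%.

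**The case against.** A paired comparison of within-block changes is valid and matches the stated outcome. Nothing here is biased, contradictory or miscalculated. That stands, and it limits the point to efficiency.

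A reader might infer that the trial is underpowered. The document does not support this. If 4.53 belongs to the difference of changes, 54 subjects already give the intended 90% for a difference of 2.0. A shortfall appears only if 4.53 belongs to the block-end difference and r is below 0.5, and the text settles neither.

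A reader might also infer that the planned analysis doubles the variance. That is the r = 0 case only. With correlation decaying over time the excess over the adjusted contrast is a factor of 1.24 to 1.59. Nor are change scores always worse than plain block-end values: they lose to them only when r is below 0.5 and win above it. The comparison that favours adjustment throughout, apart from the small price of estimating the slope, is the one with the baseline-adjusted contrast.

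The figures compare linear-model estimators, whereas the plan specifies a non-parametric paired test, so they are not the exact gain over the planned test. They are also raw-scale figures. Analysing the log of the ratio is a separate decision, and the documents give no log-scale SD to which they could be carried over.

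Finally, covariates are often left to an analysis plan. Here, however, the article itself fixes both the contrast and a test that cannot take a covariate.

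**Conclusion.** The point holds as a loss of efficiency. The primary analysis sets the slope on baseline at 1 when the data to estimate it are collected. The baseline-adjusted variance is (1 + r)/2 of the change-score variance, so the standard error falls by about 29% at r = 0 and 2.5% at r = 0.9, less about 2% of variance for the estimated slope. This rests on equal variances, the raw scale, a linear-model comparison and an r that the documents do not give. The change is worth making because it is cheap, not because the planned contrast is invalid.

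**What to change.** Make the primary analysis a regression of the within-subject difference in block-end LF:HF (weeks 6 and 24) on sequence, with the within-subject difference in block baselines (weeks 0 and 18) as covariate. With differences taken as second period minus first, the treatment effect is half the adjusted difference between sequences. Use the baseline difference itself. Entering each block's baseline as an ordinary time-varying covariate would mix between-subject and within-subject slopes. Keep the paired non-parametric test of changes as a supportive analysis.

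The cost is a change of wording, one degree of freedom and a model in place of the rank test. No visit or measurement is added. Decide separately whether to log-transform the ratio, because that changes the effect measure.

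A joint mixed model of all four values, which would keep subjects with only one block, is an alternative and not an equivalent. It would have to be reconciled with the last-observation-carried-forward rule in the Study withdrawal section.

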Evidence to date supports the safety profile of vitamin D therapy. Vitamin D deficiency is the norm in hemodialysis patients and as such, vitamin D supplementation should result in significant increase vitamin D levels. Secondly, given there is significant controversy regarding the target 25-hydroxyvitamin D level in both the general and chronic kidney disease population [38,39], we aimed to determine the effect of delivered dose of vitamin D, rather than level of vitamin D, on cardiac autonomic tone. Lastly, though there is significant practice variation, the activated and nutritional vitamin D doses chosen for the study reflect those recommended in and typically prescribed to the end-stage kidney disease population on hemodialysis [38].

Despite the high prevalence of vitamin D deficiency in ESKD, current guidelines regarding correction of vitamin D status are widely acknowledged to be opinion-based and derived from biochemical endpoints [38]. The nutritional vitamin D product (ergocalciferol) and dose proposed within this protocol is identical to that suggested by guidelines for treatment in the ESKD population [38,40]. Furthermore, treatment with other nutritional forms of vitamin D_3_ at a dose of 15,000 IU/day × 1 month [41] and 40,000 IU/day over 28 weeks, followed by 10,000 IU/day × 12 weeks [42] has been shown to be safe. A main clinical concern with activated vitamin D supplementation in the ESKD population is hypercalcemia, hyperphosphatemia and reduction in parathyroid hormone levels. This protocol employs the lowest possible dose of activated vitamin D (alfacalcidiol) available to minimize significant fluctuations in these biochemical values, though the relative importance of these changes remains unquantified within the literature [43].

In summary, the evidence to guide treatment that may minimize SCD and cardiovascular risk in ESKD is extremely limited. The VITamin D supplementation and cardiac Autonomic tone in Hemodialysis (VITAH) study is the first clinical trial to assess whether various vitamin D therapies, specifically ingestion of the combination of activated and nutritional vitamin D compared to activated vitamin D alone, influence cardiac autonomic tone and therefore cardiovascular risk in ESKD patients requiring hemodialysis.

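### The primary test is self-contradictory as named and omits the period effect of the 2×2 crossover

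*Protocol article*

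**What the plan says.** All references are to the protocol article.

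- **Primary test (Statistical analysis).** LF:HF changes are to be tested "from baseline to 6 weeks later within each treatment block utilizing a non-parametric paired t-test". No period or sequence term is mentioned for this test.
- **Further model (Statistical analysis).** The authors then write that "we will use a repeated measurements analysis of variance model to account for the cross-over design of the study". For that model, "Treatment, treatment period, and treatment sequence will be analyzed as fixed effects within the model", and the same sentence adds "additional effect modifiers (gender, vitamin D, calcium, phosphate, parathyroid hormone". It does not say at which time point these laboratory values are taken.
- **Role of the laboratory values.** Secondary outcomes lists, after the HRV measures, "as well as blood draw measurements related to vitamin D metabolism at the beginning and termination of each 6 week treatment block". The Background section on vitamin D expects vitamin D levels to rise with supplementation, and says the aim is to learn the effect of the delivered dose "rather than level of vitamin D, on cardiac autonomic tone".
- **Washout comparison (Primary outcome).** Comparing the treatment blocks with the 12-week washout "will allow for statistical interpretation of whether presence or absence of oral vitamin D therapy alters cardiac autonomic function".
- **Sample size calculation.** 54 subjects, 60 with 10% dropout, from an SD of 4.53 and a 20% larger reduction with combined therapy than with alfacalcidiol alone.

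**The concern.** Three things need to be settled before the data are seen.

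1. **Which test.** A paired t-test assesses a mean difference and a signed-rank test works on ranks. They can give different p-values on the same data. The name in the protocol allows either.
2. **Which design terms.** In a 2×2 crossover, a period effect on the 6-week change enters the intensive-minus-conventional difference with opposite sign in the two sequences. A paired test pools the sequences and leaves that effect in the error. The protocol itself introduces another model to account for the crossover, but not as the primary analysis.
3. **Which contrast and covariates.** The phrase about change within each block can be read as a before-after test per arm. The comparison with washout is not randomised either. The one model with period and sequence also carries laboratory values whose time point is open. If on-treatment values were used, the treatment estimate would lose whatever part of the effect runs through them.

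**Working it through.** **Inputs from the protocol.** SD 4.53; 54 subjects, 60 recruited; α = 0.05; the stated β = 0.9 read as power 0.90; 1:1 allocation to sequences.

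**Assumptions.** Two-sided test. Target difference 2.0, which is 20% of the baseline LF:HF of 10 in the ACE-inhibitor arm of the cited study; the protocol gives no absolute figure. The period effects, sequence imbalances and mediated shares used below are also assumed.

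**Step 1: reproduce the plan's figure.** n = (SD × (z₀.₉₇₅ + z₀.₉₀) / δ)² = (4.53 × 3.2415 / 2.0)² = 53.9, so 54; 54 / 0.90 = 60. The calculation therefore rests on the within-subject difference between treatments, with 4.53 as its SD.

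**Step 2: period effect π on the 6-week change, treatment effect τ.** The expected intensive-minus-conventional difference is τ − π in one sequence and τ + π in the other. With equal sequences the mean is still τ, but the paired test uses an inflated SD of √(4.53² + π²):

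- π = 2: √(20.52 + 4) = 4.95
- π = 3: √(20.52 + 9) = 5.43

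Putting these SDs into 3.2415 × SD / √54 moves the detectable difference from 2.00 to 2.18 and 2.40. This slightly overstates the loss, because the true standard error of the mean stays at 4.53/√54 = 0.616; only the estimated one rises (4.95/√54 = 0.674 at π = 2). That mismatch is why the test becomes conservative. A direct check at π = 2: the critical value is 2.006 × 0.674 = 1.352, and power is Φ((2 − 1.352)/0.616) = Φ(1.05) ≈ 0.85.

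Simulation with normal differences, 27 versus 27:

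| Period effect | Paired t, type I error | Paired t, power | Signed-rank, power | Period-adjusted, power |
|---|---|---|---|---|
| 0 | 0.049 | 0.889 | 0.857 | 0.889 |
| 1 | 0.042 | 0.883 | 0.865 | 0.892 |
| 2 | 0.032 | 0.850 | 0.832 | 0.890 |
| 3 | 0.020 | 0.791 | 0.752 | 0.889 |

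**Step 3: unequal sequences.** Bias has size π × |n₂ − n₁| / N.

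- 30 versus 24: 6/54 = 0.11 per unit of π, so 0.22 at π = 2 and 0.33 at π = 3. Simulated type I error of the paired t-test stays at about 0.05 or below.
- 33 versus 21: 12/54 = 0.22 per unit of π. Type I error is 0.061, 0.078 and 0.099 for π = 1, 2 and 3. The period-adjusted test stays near 0.05.

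**Step 4: laboratory covariates, if on-treatment values were used.** With a true effect of −2 and 25%, 50% or 75% of it carried through the covariate, the adjusted estimate is about −1.5, −1.0 or −0.5. If treatment shifts the covariate by 1 SD, power falls from 0.89 to about 0.39, 0.20 or 0.09. With no mediation it still falls to 0.59, because the covariate is collinear with treatment. With pre-randomisation values this problem does not arise.

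**Step 5: cost of the period term.** Power with period adjustment is 0.8895 at n = 54, against 0.8897 for the paired t-test without a period effect, and 0.92 at n = 60. Exact 90% power by the t distribution needs 56.

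**The case against.** - **Period effects may be small.** The outcome is change from each block's own baseline, so a difference in level between periods cancels; only an effect on the 6-week change matters. Recruitment runs from January 2013 to 2016. If enrolment is spread over those years, each period covers all seasons, and season adds noise rather than a systematic period effect. Subjects without the 4-week washout are those taking no vitamin D at enrolment. This stands: the protocol does not establish that a period effect is likely, and the 2 units assumed above equal the whole target difference.
- **Bias is a remote case.** Starting from 30 per sequence, 30 versus 24 means all six expected dropouts fall in one sequence, despite 1:1 allocation in small blocks. Withdrawn subjects' data are also to be carried forward, so unequal completion need not become unequal analysed sequences. This stands too. A reader might infer that the paired test is biased or invalid without a period term; the documents do not support that.
- **Over-adjustment is not stated.** The laboratory values are called effect modifiers, have no stated time point and sit outside the primary test. A reader might infer that the plan adjusts for treatment-affected values; the text leaves this open. The protocol links changes in calcium, phosphate and PTH to activated vitamin D, which is the same in both arms. Vitamin D level is the one clearly expected to differ.
- **The contrast is clear elsewhere.** Study aims and the sample size section both compare intensive with conventional therapy. That makes the before-after reading the less likely one, but the analysis sentence should say so itself.

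None of this resolves the contradictory test name or supplies the missing period term. An unseen analysis plan may do both, but the published wording would still need correction.

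**Conclusion.** The point holds in a limited form. The primary test is not identifiable from its name, and under either reading it omits period in a 2×2 crossover. With balanced sequences the consequence is lost efficiency and a conservative test: power about 0.89 to 0.85 at an assumed period effect of 2 units, and to 0.79 at 3. Bias is conditional on a period effect together with unequal sequences. These sizes rest on the assumed target difference of 2.0, normal differences and assumed period effects; the protocol supplies no estimate of a period effect.

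The covariate problem is also conditional. It arises only if on-treatment values enter the further model, above all 25OHD, and it would then run against the stated aim of estimating the effect of dose. It does not touch the primary p-value as planned. Before-after changes per arm and the treatment-versus-washout comparison are not randomised contrasts and cannot carry the trial's conclusion.

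**What to change.** - **Primary analysis.** Name one: the intensive-minus-conventional difference in LF:HF change from block baseline (weeks 0 to 6 and 18 to 24), from a crossover model with treatment, period and sequence as fixed effects and subject as random. Report the estimate with a 95% CI on the scale used for the sample size.
- **Non-parametric sensitivity analysis.** Use a Wilcoxon rank-sum test comparing within-subject period differences between the two sequences. This allows for period, which a signed-rank test does not.
- **Effect modifiers.** In the repeated-measures model, use only pre-randomisation vitamin D, calcium, phosphate and PTH. Table 3 already collects all four at screening.
- **Descriptive results.** Label before-after changes per arm and the washout comparison as descriptive.

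The cost is a change of protocol or analysis-plan wording and about one degree of freedom. No new data are needed, and 54/60 remains adequate, with power of 0.89 at 54 and 0.92 at 60 under the assumptions above.
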